#### Hip Circumference

Hip circumference will be measured at the largest level of the symphysis pubis and gluteus maximus. The tape should be in contact with the skin but not compress soft tissue, and twists in the tape should be avoided. The participants should be required to breathe normally. The same measuring tape should be used throughout the trial. Hip circumference will be recorded to the nearest 0.1 cm.

---

### Waist-to-hip Ratio

We will obtain the waist-to-hip ratio through waist circumference divided by hip circumference.

### Waist-to-height Ratio

We will obtain the waist-to-height ratio through waist circumference divided by height.

### Systolic and Diastolic Blood Pressure

Blood pressure measurements were performed with a calibrated Omron U30 electronic sphygmomanometers in the sitting position. Strictly following the American Heart Association's Standardized protocol, measurements should be taken with an interval of minimum 5 minutes of the rest for the participants in a quiet setting without distractions. The second two readings will be averaged to be recorded as the systolic or diastolic blood pressure.

### Demographic Information and Health Related Questions

For descriptive purposes, the following participant socio-demographic characteristics, including sex (male/female), age, education level (illiterate, elementary, middle school, high school or above), marital status (married, never married, widowed, divorced), household income (<12000 RMB, 12000-19999 RMB, 20000-59999 RMB,  $\geq$  60000 RMB), and employment (yes/no) will be collected at baseline.

Health behaviors including smoking status (never, former, current), alcohol consumption (never/seldom, < once a month,  $\geq$  once a month, daytime napping (0, 1-60 minutes/day, over 60 minutes/day) will also be obtained at baseline.

Self-reported medical history, including hypertension, diabetes mellitus, asthma, coronary heart disease, chronic bronchitis/emphysema, psychiatric disorders, and malignant tumors will be collected at baseline.

### Adverse Events

---

A surveillance form will be used to screen for adverse events (AEs) and serious adverse events at each assessment visit (see Appendix A). Serious, unexpected AEs that are related or are possibly related to the study will be reported to the Institutional Review Board (IRB) immediately.

### **Qualitative Interviews**

We will obtain oral consent from each participant prior to the beginning of each interview. All interview will be recorded and transcribed. We will use RE-AIM to identify the domains, including: (1)Reach, participant perception of the program recruitment process; (2)Efficacy, is the intervention benefits for improving health benefits, the impact of intervention on participants; (3)Adoption, participants' evaluation of the adoption of each intervention; (4)Implementation, participants' satisfaction with the intervention program as a whole; (5)Maintenance, participants' willingness to continue performing PA after the end of the intervention and their overall attitude toward PA before and after the intervention.

### **Outcomes**

Our primary outcome is the changes in leisure-time activity at 8 weeks. Our secondary outcomes include household activity, work-related activity, total PA, proportions of meeting WHO recommendations, leisure-time preferences, sedentary behavior, self-efficacy, self-regulation, self-rated health, cognitive function, night-time sleep quality, weight, percentage weight change, body mass index, percentage body fat, visceral fat, waist circumference, hip circumference, waist-to-hip ratio, waist-to-height ratio, and systolic and diastolic blood pressure at all assessment time, as well as the leisure-time activity at 4 weeks, 6 months, 12 months, and 24 months.

---

## **Quality Assurance and Control**

Quality assurance and quality control are of paramount importance in a randomized controlled trial. Standardized protocols for all measurements have been developed, and adherence to the written protocols is of utmost importance. All data collection personnel will be certified as competent to make the required measurements by trained experts. The following is a summary of the quality assurance and control program:

### **1. Personnel**

Quality control of personnel is carried out in three main areas: a) Staff in surveys, interviews, and telephone counseling will be trained by professionals, with unified technical standards. b) Clear division of jobs, e.g. logistics during the investigation and coordination of personnel on site will be handled by different people. c) Responsibilities will be clearly defined, e.g. a person will be responsible for the safekeeping and storage of questionnaires.

### **2. Research Instruments**

a) The study proposes to use internationally recognized research methods and tools (such as the PASE) to ensure the quality of the data. b) Intervention materials (e.g. dissemination materials) are developed by a team member specializing in physical education and sport, in consultation with relevant experts and with reference to national and international standards, in order to ensure the correctness and traceability of knowledge.

### **3. Quality Management System**

a) Develop and implement a quality control program within the project team to ensure quality control at each key stage. b) Establish good external communication and feedback mechanisms with the team leaders of the peer groups and key figures of the villages to implement quality control.

---

## **Data Management and monitoring**

Face-to-face interviews will be conducted to collect data by eligible assessment team at baseline, 4 weeks, 8 weeks, 6 months, 12 months, and 24 months after the baseline. The collected data will be transferred from paper form to electronic record through data entry by study personnel. Standardized approaches will be used to ensure the high-quality of data. Selected project managers will build the electronic database. Confidentiality of the database will be protected by using password-protected computers. Only those designated by the project manager can access the data using the encrypted computers under the supervision of management. The staff are trained to comply with and use protected health information.

The study team will conduct monthly quality monitoring checks. The database will only be shared among the study team. Emails will be encrypted if data will be sent between the project staff, however, emails will be minimized.

---

## Sample Size Computation

Based on the prior PA intervention meta-analysis, the sample size required for each group was estimated to be about 90 with a power of 80%, an  $\alpha$  of 0.05, and assumed an effect size of 0.42. Because the randomization occurs at the village level, we need to consider the clustering effect.

The sample size (SS) for a clustered RCT is defined by equation (1):

$$SS_{\text{cluster RCT}} = SS_{\text{standard RCT}} \times DE \quad (1)$$

The design effect (DE) is obtained from equation (2):

$$DE = 1 + (n-1) \times ICC \quad (2)$$

$$\text{Where: } ICC = \frac{\sigma_{\text{between}}^2}{\sigma_{\text{between}}^2 + \sigma_{\text{within}}^2} \quad (3)$$

and  $n$  = cluster size (number of participants per cluster)

In equation (3),  $\sigma_{\text{between}}^2$  is the between-cluster variance for the outcome measure and  $\sigma_{\text{within}}^2$  is the within-cluster variance for the outcome measure.

We conducted a pilot study prior to the SAWA to calculate the DE. With a DE of 2.1, we will need a sample size of 189 ( $90 \times 2.1$ ) for each group after factoring in the cluster effects. Taking participation attrition into account, we will screen 20% more participants. Each group will have 227 participants, so the total sample size will be 454 participants for the two groups (intervention group and control group).

---

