## Overview of Trial Design

### Design

This study is a single-blinded cluster randomized controlled trial to test the effect and sustainability of the multilevel PA intervention to improve PA levels in rural older adults. There were 8 villages participating in total: 4 intervention sites and 4 control sites. RE-AIM (Research, Efficacy, Adoption, Implementation, and Maintenance) will be applied to evaluate the pre-post and intervention-control differences as well as external validity.

[figure not shown]

---

Figure 1. Overview of SAWA Intervention

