## **Data Analysis Plan**

### **1. Primary Analyses**

The primary aim will be to assess the leisure-time activity level at 8 weeks in the context of linear mixed model effects multilevel models. In this analysis, the intention-to-treat approach will be used. In addition to the intervention group, assessment time, and their interaction terms, the model may include individual-level (age, sex) variables as explanatory covariates. A random village intercept term is included to account for clustering by villages. The primary study hypothesis of SAWA will be tested based on a two-tailed significance level of 0.05.

An intention-to-treat analysis that includes all randomized participants, regardless of the number of assessments obtained, will be conducted. The analytical plans are flexible and will be adapted as scientific perspectives are advanced.

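### The stated 80% power ignores that there are only four villages per arm; on 6 degrees of freedom the plan's own inputs give about 65% to 73%.

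*Supplement*

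**What the plan says.** All references are to the final protocol in the Supplement.

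- **Design:** "There were 8 villages participating in total: 4 intervention sites and 4 control sites".
- **Sample Size Computation:** "the sample size required for each group was estimated to be about 90 with a power of 80" per cent, two groups, alpha 0.05; the authors "assumed an effect size of 0.42". Then "With a DE of 2.1, we will need a sample size of 189" per group. Then "Taking participation attrition into account, we will screen 20% more participants", which gives 227 per group and 454 in all. The design effect formula depends on cluster size and the ICC. The design effect is attributed to a pilot study, but neither quantity is given a number.
- **1. Primary Analyses:** a linear mixed model with group, assessment time and their interaction, optional age and sex, and a random village intercept. "The primary study hypothesis of SAWA will be tested based on a two-tailed significance level of 0.05". No degrees-of-freedom method is named.
- **Outcomes:** the primary outcome is the change in leisure-time activity at 8 weeks.

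**The concern.** Multiplying an individually randomised sample size by a design effect puts the right variance under the treatment difference. It keeps a reference distribution that assumes this variance is known, or is estimated from many units. Here the between-village part is estimated from eight villages in two arms, which leaves 8 − 2 = 6 degrees of freedom and a two-sided 5% critical value of 2.447 instead of 1.96.

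Two things are at stake. If the trial's real power is below 80%, a null result will be read as firmer evidence of no effect than it is. And because the primary test is not tied to a reference distribution that reflects eight villages, the trustworthiness of its p-value is open.

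**Working it through.** **Inputs.** From Sample Size Computation: effect size d = 0.42 (SD 1), 80% power, design effect DE = 2.1, 189 per arm needed, 227 enrolled. From 1. Primary Analyses: two-sided alpha 0.05. From Design: 4 villages per arm.

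**1. The plan's own figures reproduce.**
- n per arm = 2(1.960 + 0.842)²/0.42² = 89.0 by the normal approximation. With a t-test on 178 df, n = 90 gives 80.0% power.
- 90 × 2.1 = 189, and 189 × 1.2 = 226.8, rounded to 227.
- Power at 189 per arm with DE 2.1 and a normal reference: 80.4%.

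The arithmetic is sound. The assumption about the reference distribution is what fails.

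**2. Same inputs on 6 df.**
- Effective n per arm = 189/2.1 = 90.
- Noncentrality = 0.42 × √(90/2) = 2.817.
- P(|t₆(2.817)| > 2.447) = 65.4%. A simulation of 400,000 comparisons of 4 v 4 village means agrees (65.4%).
- Solving for 80% power at the same n gives d of about 0.50 (d = 0.50 gives 79.7%).

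**3. All 227 per arm analysed.** This is 56.75 per village, and the result depends on the village size at which DE = 2.1 was obtained, since ICC = 1.1/(m − 1).

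| DE 2.1 taken at m = | ICC | DE at 56.75 | Effective n per arm | Power, 6 df |
|---|---|---|---|---|
| 47.25 (189/4) | 0.0238 | 2.33 | 97.6 | 68.8% |
| 56.75 (227/4) | 0.0197 | 2.10 | 108.1 | 73.1% |

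**4. Pilot cluster size unknown (assumption, range shown).** With 189 analysed per arm (47.25 per village):

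| DE 2.1 taken at m = | ICC | DE at 47.25 | Power, 6 df |
|---|---|---|---|
| 22.5 | 0.051 | 3.37 | 46% |
| 47.25 | 0.024 | 2.10 | 65% |
| 56.75 | 0.020 | 1.91 | 69% |
| 100 | 0.011 | 1.51 | 79% |
| 150 | 0.007 | 1.34 | 83% |

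**5. Baseline adjustment (assumption).** Suppose baseline explains r² of the variance both between and within villages. The noncentrality is then 2.817/√(1 − r²). With 189 per arm this gives 69% for r = 0.3, 77% for r = 0.5 and 83% for r = 0.6. The documents give no r.

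**6. What the specified model does with villages.** A random village intercept shifts all visits of a village by the same amount. In the group-by-time contrast, the 8-week mean minus the baseline mean, that shift essentially cancels. The standard error of change then rests on residual variation between observations, and a Kenward-Roger correction applied to that model would return residual degrees of freedom, not about 6. Villages that differ in how much they change are not represented.

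**7. A large-sample reference on village-level data.** P(|t₆| > 1.96) = 9.8%, so a z-test of a 4 v 4 comparison of village means would have about twice the nominal 5% type I error.

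**The case against.** The strongest reply is that 65% is one conditional value. It takes DE 2.1 as exact at 47 per village and ignores the baseline visit, although the outcome is a change and the model includes baseline. A baseline correlation near 0.6, or a pilot design effect measured in villages of about 150, would bring power above 80%. This stands as a limit on precision. It does not rescue the stated figure, because the sample size section claims no gain from baseline, gives no correlation and does not report the pilot cluster size.

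A reader might infer that power could be as low as 46% and treat that as a finding. The documents do not say that the pilot used 22 or 23 people per village; that value is only one end of an assumed range whose other end is 83%.

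A reader might also infer that the planned primary test has a 9.8% false-positive rate. That figure belongs to a z-test on village means. The plan names neither z nor t, and its model is not a village-means comparison, so the figure warns against one way of completing the specification and does not describe the planned test.

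Two related points are clarifications at most. The protocol promises to screen 20% more, not to withstand 20% loss, and 189 × 1.2 does what it says. It covers 1 − 189/227 = 16.7% loss; withstanding 20% would take 189/0.8 = 236.25, or 237 per arm. Losing 20% of 227 would change power little (64.6% against 65.4%). And the 0.42 and the 2.1 may not suit the leisure-time score, but the text does not say which activity measure either refers to, so a mismatch is not shown.

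**Conclusion.** The concern holds in this form. The 80% in the sample size section is the power of a comparison with many degrees of freedom, and the trial has eight villages. On the plan's own inputs the figure is about 65% at the planned analysed size and 69% to 73% with no loss. This assumes equal village sizes (unequal sizes would lower it), DE 2.1 holding at 47 to 57 per village, and no baseline adjustment. Power at or above 80% is possible only under assumptions the plan neither states nor supports. Separately, the primary model as written does not carry village variation in change, so the few-village problem is unaddressed in the test as well as in the power statement.

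**What to change.** **Sample Size Computation.** Keep the enrolment. Replace the power claim with wording such as: with four villages per arm and a design effect of 2.1, power for an effect size of 0.42 is about 65% (189 analysed per arm) to 73% (227 analysed per arm) on 6 degrees of freedom; with 189 per arm, 80% power applies to an effect size of about 0.50. Report the pilot ICC and the cluster size behind the 2.1. If credit for baseline adjustment is wanted, state the correlation and its source.

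**1. Primary Analyses.** Make the 8-week test reflect village variation in change, by one of two routes:
- add a village-by-time random effect and name a small-sample degrees-of-freedom method (Kenward-Roger or Satterthwaite); or
- compare village-level, baseline-adjusted changes between arms on t with 6 degrees of freedom.

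Naming Kenward-Roger while keeping only the random village intercept would not achieve this.

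**Optional clarification.** State that 227 per arm covers 16.7% loss, and which activity measure the effect size and design effect refer to.

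**Cost.** One reworded paragraph, pilot figures from the study the protocol says was done, and a few lines of test specification. No extra participants or villages. The stated power is less favourable and the interval is wider: for a given standard error, by 2.447/1.960, about 25%.

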## **Data Analysis Plan**

### **1. Primary Analyses**

The primary aim will be to assess the leisure-time activity level at 8 weeks in the context of linear mixed model effects multilevel models. In this analysis, the intention-to-treat approach will be used. In addition to the intervention group, assessment time, and their interaction terms, the model may include individual-level (age, sex) variables as explanatory covariates. A random village intercept term is included to account for clustering by villages. The primary study hypothesis of SAWA will be tested based on a two-tailed significance level of 0.05.

An intention-to-treat analysis that includes all randomized participants, regardless of the number of assessments obtained, will be conducted. The analytical plans are flexible and will be adapted as scientific perspectives are advanced.

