#### Physical Activity

The PA level of participants including leisure-time activity, household activity, work-related activity, and total PA will be measured by the Physical Activity Scale for the Elderly (PASE), a widely used instrument for older adults. Previous studies demonstrated the validity and reliability of the scale for assessing the PA level of older adults in the Chinese population. The score of each item of the PASE is calculated by multiplying the weight and frequency. The total PA score is the sum score of the leisure-time activity, household activity, and work-related activity. The primary outcome is the changes in leisure-time activity at 8 weeks, and the other two domains of PA and total PA are the secondary outcomes.

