### **2. Secondary Analyses**

#### **a. Handling of missing data**

Although substantial effort will be employed to minimize missing data, it is inevitable that some missing data will occur. Missing data are expected due to drop outs and missed visits. The leisure-time activity level is a subject-level variable and missing assessments would influence tests relative to treatment-by-time interactions. The primary analysis described above will be conducted within each dataset using linear mixed effect models and employ restricted maximum likelihood using all available data. Results of datasets will be combined to produce final estimates for between-group comparisons. This approach assumes data are missing at random: the mechanism that gives rise to missing data relies on observed data only. To assess the sensitivity and robustness of the results, we will compare results of two sets of analyses: i) all participants, with or without missing data, were subjected to the repeated measures linear mixed model analysis; ii) we will perform the linear mixed model with missing

---

data imputed using multiple imputation.

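### The final plan does not fix which 8-week contrast is the primary test or how the baseline leisure-time score enters the model, and it leaves age and sex optional

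*Supplement*

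**What the plan says.** All references are to the final protocol in the Supplement.

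- **Outcome.** Under Physical Activity: "The primary outcome is the changes in leisure-time activity at 8 weeks". Under Outcomes: "Our primary outcome is the changes in leisure-time activity at 8 weeks".
- **Primary analysis.** Under Data Analysis Plan, 1. Primary Analyses: "The primary aim will be to assess the leisure-time activity level at 8 weeks". The model has group, assessment time and their interaction. On clustering: "A random village intercept term is included to account for clustering by villages". No participant-level term is named.
- **Covariates.** The same section says that "the model may include individual-level (age, sex) variables as explanatory covariates". Neither there nor elsewhere in the Data Analysis Plan is the baseline leisure-time score named as a covariate, although Data Collection lists baseline among the assessments.
- **Latitude.** The section closes with: "The analytical plans are flexible and will be adapted as scientific perspectives are advanced".
- **Indirect evidence on baseline.** In 2. Secondary Analyses, a. Handling of missing data, all participants "were subjected to the repeated measures linear mixed model analysis", and missing visits are discussed for their effect on tests of treatment by time. Under b. Secondary Outcomes, baseline is listed with the other visits, and continuous secondary outcomes follow a strategy similar to the primary one.

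No sentence says whether baseline is a level of assessment time, or which coefficient or contrast gives the primary p-value.

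**The concern.** Two analyses fit this text. One takes the group-by-time term at 8 weeks, with baseline as a visit, and estimates a difference in change. The other compares arms on the 8-week score. They are different estimators of the same effect, and they separate by exactly the baseline difference between the arms. Four villages per arm are allocated, and Randomization describes no stratification or matching, so some baseline difference is to be expected.

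Two things are at stake. First, the contrast and the covariates could be chosen after the baseline difference is known, and the flexibility sentence permits it. Second, precision is lost: for any positive r below 1, either contrast has a larger individual-level variance than an analysis that adjusts for the baseline score.

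**Working it through.** **1. The plan's own figure.** Inputs from Sample Size Computation: effect 0.42 SD, 80% power, two-sided 0.05 (sidedness from 1. Primary Analyses), design effect 2.1, 20% added. The normal formula gives 2 × (1.960 + 0.842)² / 0.42² ≈ 89 per arm; the t-based version gives 89.96, so 90. Then 90 × 2.1 = 189, 189 × 1.2 = 226.8, so 227, and 2 × 227 = 454. All stated figures reproduce. None uses a baseline correlation.

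**2. What the group-by-time term estimates.** In a small simulation (60 complete data sets, 8 villages of 48, r = 0.5, intraclass correlation 0.024, baseline and 8-week rows, village intercept only), the interaction equalled the difference in mean change to rounding error. With no participant term, its average model standard error was 0.142 against an empirical 0.111.

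**3. Size of a chance baseline difference.** If design effect 2.1 applies at baseline, the standard error is √(2 × 2.1 / 189) = 0.149 SD, and 0.149 / 0.42 = 35% of the assumed effect. At 227 per arm it is 0.136 SD (32%). At 189 per arm, a difference of at least 0.15 SD arises in about 31% of allocations and of at least 0.20 SD in about 18%.

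**4. What each reading does with a difference of 0.149 SD.** Equal SDs at both visits are assumed. The documents give no r, so a range is shown. Level carries r × 0.149; change is off by −(1 − r) × 0.149.

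| r (assumed) | shift, level | shift, change |
|---|---|---|
| 0.3 | +0.045 | −0.104 |
| 0.5 | +0.075 | −0.075 |
| 0.7 | +0.104 | −0.045 |

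The two estimates differ by 0.149 SD whatever r is.

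**5. Precision.** Individual-level variance factors are 1 for level, 2(1 − r) for change and 1 − r² for baseline-adjusted. Power is at 189 per arm by normal approximation with the design effect held at 2.1. It is for comparison between rows only, because it ignores the few degrees of freedom that 8 villages give.

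| r (assumed) | level: factor, power | change: factor, power | adjusted: factor, power | adjusted / change | adjusted / level |
|---|---|---|---|---|---|
| 0.3 | 1, 80% | 1.40, 66% | 0.91, 84% | 0.65 | 0.91 |
| 0.5 | 1, 80% | 1.00, 80% | 0.75, 90% | 0.75 | 0.75 |
| 0.7 | 1, 80% | 0.60, 95% | 0.51, 98% | 0.85 | 0.51 |

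**6. How far this carries to villages.** With 189 / 4 = 47.25 per village, the design effect implies an intraclass correlation of 1.1 / 46.25 = 0.024. The between-village share of an arm mean's variance is then 47.25 × 0.0238 / 2.1 ≈ 0.535. So about half of the variance depends on a village-level correlation that the documents do not give. If it were 0.9 with an individual r of 0.5 (both assumed), the combined slope would be 0.535 × 0.9 + 0.465 × 0.5 ≈ 0.71. A difference of 0.15 SD would then shift level by +0.107 and change by −0.043, in place of a symmetric 0.075.

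**The case against.** The best defence is that the plan, read as a whole, already has a coherent primary test. It specifies group, time and their interaction, calls the model repeated-measures, ties missing data to treatment-by-time tests and lists baseline among the visits. On that reading the 8-week interaction is the difference in change, as the outcome definition says. The word level may only be the name of the variable, since the section on missing data uses it that way.

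Most of this stands, and it is why change is the likely reading. It also rules out the stronger inference that the plan ignores baseline and leaves chance imbalance untouched. That would be right only if baseline were left out of the time factor, and the documents do not say so. What the defence does not supply is a sentence that fixes the contrast, and under it the change contrast still over-corrects a given imbalance.

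Three further limits are fair:

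- Over randomisation neither contrast is biased; the shifts are conditional on an observed imbalance.
- The variance ratios are individual-level and rest on an assumed r.
- A reader might infer that the flexibility sentence voids the 0.05 level. It allows a data-dependent choice, but no inflation of type I error has been calculated, and none is claimed.

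**Conclusion.** The point holds as a gap in specification with a gain in precision on offer. The final plan does not name the primary contrast or the role of the baseline score, and its covariates are optional under a clause that allows later adaptation. The candidate estimates differ by the chance baseline difference, whose standard error is about 0.149 SD, or 35% of the assumed effect, if design effect 2.1 holds at baseline. Baseline adjustment would cut individual-level variance by 35%, 25% and 15% against change, and by 9%, 25% and 49% against level, at assumed r of 0.3, 0.5 and 0.7. The realised gain may be larger or smaller, because the village-level correlation is unknown. The documents do not support saying that the planned estimate is biased or that baseline goes unused. The change should be made; the plan can be run without it, but its primary p-value would not be tied to one model.

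**What to change.** In Data Analysis Plan, 1. Primary Analyses, name one model:

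- **Estimate:** the between-arm difference in leisure-time score at 8 weeks, from a linear mixed model of the post-baseline visits.
- **Fixed effects:** group, visit, group by visit, the participant's baseline leisure-time score, age and sex. Replace the optional wording on covariates by a firm statement that they are included.
- **Random effects:** village intercept and participant intercept. A stated residual covariance could take the place of the participant intercept, but one of the two must be chosen now.
- **Later changes:** replace the flexibility sentence by a statement that any change made after 8-week data have been seen by arm is reported as post hoc.

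With the baseline score as a covariate, level and change give the same treatment effect, because subtracting baseline from the outcome alters only the baseline coefficient. The wording mismatch then no longer matters. Continuous secondary outcomes should use their own baseline in the same way (baseline weight for percentage weight change).

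The cost is wording only, since every variable is already collected. One consequence needs a sentence: participants with no post-baseline visit contribute nothing to this model, so the text should say that they enter through the multiple-imputation analysis already planned.
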